## Abstract

**Background:**

Skeletal muscle serves as the primary source of power for body movement. Due to the transition of menopause, older women experience a relatively faster decline in skeletal muscle mass and function, making them more susceptible to age-related skeletal muscle disorders such as sarcopenia, which can lead to adverse outcomes such as falls, fractures, disability, or even death. Blood flow restriction low-intensity resistance training (LI-BFRT) can effectively enhance muscle strength and promote skeletal muscle growth, while repetitive transcranial magnetic stimulation (rTMS) has previously been shown to improve motor cortex excitability and limb motor function. We describe a trial protocol to investigate the effects of a 12-week intervention combining rTMS with LI-BFRT on skeletal muscle mass and physical function in community-dwelling postmenopausal women.

**Methods:**

This single-blind, randomized controlled trial will recruit 54 eligible community-dwelling postmenopausal women aged 50–65 years who have been naturally postmenopausal for 1 year or more. Participants will be randomly assigned in a 1:1:1 ratio to the rTMS combined with the blood flow restriction low-intensity resistance training group (rTMS + LI-BFRT), the blood flow restriction low-intensity resistance training group (LI-BFRT), and the control group, respectively, for a 12-week intervention period. Participants will undergo assessments at baseline (Week 0), immediately after the intervention (Week 12), and long-term follow-up (Week 24). The primary outcomes include lower limb muscle mass, muscle strength in both the upper and lower limbs; secondary outcomes include body composition, physical function (5-time sit-to-stand test, 30-second stand test, timed up-and-go test, 30-second arm curl test), motor cortex excitability, and clinical blood markers related to neural and muscular function.

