**Figure 1 F1:**
[figure not shown]
Flow chart showing the participant recruitment, intervention and assessment process. LI-BFRT, low intensity-blood flow restriction training; rTMS, repetitive transcranial magnetic stimulation; 1RM, 1 repetition maximum.

This study recruited healthy postmenopausal women. After applying inclusion and exclusion criteria, eligible participants were randomly assigned to the rTMS + LI-BFRT group, LI-BFRT group, and control group in a 1:1:1 ratio. Researchers confirmed the basic information of all participants who had signed informed consent forms (age, date of birth, contact information); after confirmation, blood samples were collected from participants, and height, weight, and body composition were measured. Subsequently, tests were conducted to assess skeletal muscle mass, skeletal muscle strength, motor cortex excitability, and motor performance. Participants in the two intervention groups received a 12-week supervised training intervention, three times per week. The control group was instructed to maintain their previous lifestyle and undergo a 12-week health education program, once per week. The program comprises weekly lectures on general health topics (nutrition, sleep hygiene, chronic disease awareness) and explicitly does not include active physical training or exercise prescriptions. All participants were assessed at three time points: pre-intervention (Week 0), post-intervention (Week 12), and at long-term follow-up (Week 24). The intervention and assessment schedule are outlined in Table 1.

**Table 1 T1:** The schedule of participant recruitment, intervention, and study assessment.

Variables	Recruitment and screening	Baseline assessment	Intervention (Week 1-Week12)		Follow-up assessment	Long-term Follow-up assessment
Time-point		Week 0	Week 4	Week 8	Week 12	Week 24
Information consent	X					
Inclusion and exclusion criteria	X					
Demographic data	X					
Randomization	X					
AOP test		X				
RMT test		X				
Resistance training load		X	X	X		
Primary outcomes						
Thigh muscle CSA		X			X	X
Calf muscles CSA		X			X	X
Hand grip strength		X			X	X
Knee extension MVC		X			X	X
Secondary outcome						
Body composition		X			X	X
5-times chair stand test		X			X	X
30-Second Chair Stand test		X			X	X
Timed Up and Go test		X			X	X
30-Second Arm Curl Test		X			X	X
MEPs test		X			X	X
Hematological parameters		X			X	X

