##### Muscle cross-sectional area (CSA)

2.6.1.1

CSA is diagnosed by an experienced radiologist. Lower limb muscle cross-sectional area is measured using a CT spiral scanner (uCT520, United Imaging Medical Technology Co., Ltd, Shanghai, China). Patients are instructed to lie in a supine position, ensuring that the CT scan plane is perpendicular to the coronal plane of the lower limbs. The scanning regions include: the thigh muscle cross-sectional area, the midpoint of the line connecting the greater trochanter of the femur and the lateral condyle of the femur (40), the calf muscle cross-sectional area, the midpoint and the upper third of the line connecting the inferior border of the patella and the lateral malleolus (41).

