##### Muscle strength

2.6.1.2

Grip strength, which represents upper limb strength, was measured using a handheld grip dynamometer (JAMAR smart, USA). Participants sat with their elbows flexed at 90° and their upper limbs immobilized while holding the grip dynamometer. Upon receiving the “start” command, they gripped the inner and outer handles with maximum force, and the peak grip strength was recorded. Three measurements were taken for each hand. There was a one-minute interval between each measurement, and the final result was the maximum value of the three measurements. Measure the maximal voluntary contraction (MVC) of knee extension of the lower limbs using a portable muscle strength tester, micro FET3 (Hoggan Health Industries, USA). During the test, the subject sat on a chair or bed with both feet suspended in the air, the hip and knee joints flexed at 90°, and the tester held the device in front of the subject's lower leg near the ankle joint. Upon the “start” command, the participant performed knee extension with maximum force, while the tester applied resistance using the portable muscle strength tester micro FET3 for 4 s, recording the peak muscle strength.

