### Statistical analysis

2.8

All data were analyzed using SPSS Statistics version 26 (SPSS Inc., USA). Continuous variables are presented as mean ± standard deviation. Baseline characteristics were compared using one-way ANOVA for normally distributed data or the independent-samples rank-sum test/chi-square test for non-normal or categorical data. Intervention effects over time were assessed using two-way repeated-measures ANOVA (time × group) across three time points (baseline, post-intervention, and long-term follow-up). Significant interactions were followed by Bonferroni-corrected pairwise comparisons. Pearson correlation was used to explore relationships between changes in cortical excitability, serum biomarkers, and muscle mass or functional outcomes. Potential synergistic effects of rTMS and LI-BFRT were further evaluated using factorial ANOVA, with significance set at *P* < 0.05.

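### Four primary outcomes are each tested at 0.05 with no rule across them, so the chance of at least one false-positive primary result is about 9–19% if any one significant interaction counts as success

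*Protocol article*

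**What the plan says.** The abstract names several primary outcomes together: "The primary outcomes include lower limb muscle mass, muscle strength in both the upper and lower limbs". Table 1 (section 2.1) puts four rows under its primary heading: "Thigh muscle CSA", "Calf muscles CSA", "Hand grip strength" and "Knee extension MVC". Each is measured at Weeks 0, 12 and 24.

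Two of these rows could yield more than one variable. Section 2.6.1.1 scans the calf at "the midpoint and the upper third of the line connecting the inferior border of the patella and the lateral malleolus". For grip, section 2.6.1.2 says "Three measurements were taken for each hand". Neither section says how the levels or the hands are combined.

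Section 2.8 plans a time × group repeated-measures ANOVA over the three visits, with significance at P < 0.05. Its only multiplicity rule is "Significant interactions were followed by Bonferroni-corrected pairwise comparisons". Section 2.7 bases the sample size on one one-way ANOVA at 0.05 and does not say which outcome it refers to.

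**The concern.** The Bonferroni step works inside one outcome, and only after that outcome's interaction is significant. Nothing links the four outcomes: there is no lead outcome, no testing order, no division of alpha and no requirement that all four succeed. A trial reported under this plan could present any one significant primary as a positive result. Readers would take that result to carry a 5% risk of error, when 5% is only the risk for each test.

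The number and ranking of primary outcomes is the protocol's own decision, so this concerns what the document fixes and is more than an omitted detail.

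**Working it through.** **Inputs from the protocol.** Four primary outcomes (Table 1); P < 0.05 and a time × group test (section 2.8); three equal arms, f = 0.4, target power 0.95, N = 42 before attrition and 54 recruited (section 2.7). N = 42 is 14 per arm.

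**Assumed inputs.** The correlation between primary outcomes is not given, so a common value from 0 to 0.9 was used. Within-person correlation over time was set at 0.7.

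**The plan's own figure.** The protocol states no family-wise error rate to reproduce. Its sample size does not reproduce as described: a one-way ANOVA with three groups, f = 0.4, alpha 0.05 and power 0.95 needs N = 102. N = 42 is the answer for f = 0.65, the value that section 2.7 sets aside. That is a separate matter, but it affects the power figures in step 4.

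**Step 1: independent outcomes.** The chance of at least one false positive in m tests is 1 − 0.95^m.
- m = 4: 1 − 0.95^4 = 1 − 0.8145 = 18.5%
- m = 5: 1 − 0.95^5 = 1 − 0.7738 = 22.6%

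**Step 2: correlated outcomes, planned test.** The time × group F test at 0.05 was simulated under the global null (14 per arm, three visits). The table gives the chance that at least one interaction is significant; ranges span repeat runs.

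| Assumed correlation | Four outcomes | Five outcomes |
|---|---|---|
| 0 | 18.4–18.8% | 22.2–22.5% |
| 0.3 | 17.5% | 21.6% |
| 0.5 | 16.0–16.4% | 18.8–19.6% |
| 0.7 | 13.2–14.1% | 15.5–16.1% |
| 0.8 | 12.2% | 13.5% |
| 0.9 | 9.2–10.3% | 11.2% |

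**Step 3: a Bonferroni-significant pair also required.** Four outcomes, correlation 0 to 0.7:
- arms compared on change from baseline: 13.9% falling to 10.6%
- times compared within an arm: 14.1% falling to 10.7%
- arms compared on raw values at Week 12 or 24: 3.6% falling to 2.9%

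**Step 4: effect of a correction.** Splitting alpha over four tests gives 0.05 / 4 = 0.0125, which is also the first Holm step. The family-wise rate is then 1 − 0.9875^4 = 4.9% for independent outcomes, and 4.6% simulated at correlation 0.5. One-way ANOVA power for f = 0.4:

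| Alpha | N = 42 | N = 54 | N for 95% power |
|---|---|---|---|
| 0.05 | 60% | 73% | 102 |
| 0.0125 | 37% | 51% | 132 |

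**The case against.** **A separate analysis plan may supply the rule.** The article is condensed, and section 2.8 does not say that no further adjustment will be made. This has some weight. But section 2.8 does fix the level and says where Bonferroni applies, and the protocol itself chose four unranked primaries.

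**The inflation rests on a success rule that the protocol never states.** This stands. The planned sequence could be read as needing both a significant interaction and a significant pair. The rate then falls to about 11–14% on change scores, and to 3–4% on raw between-arm values. The protocol specifies neither the contrast nor the rule, so it does not secure the lower figure.

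**The outcomes may be closely related.** This also stands, as a limit on size. The documents give no correlation, and at 0.9 the four-outcome rate is 9–10%, still about twice 5%.

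Three stronger readings are tempting, and the documents do not support them:
- A reader might count at least five primaries because of the two calf levels. Table 1 has one calf row, and the levels could be combined.
- A reader might say that the correction covers pairs of arms only. Section 2.8 does not say whether the pairs are arms, times or both.
- A reader might say that the protocol promises a 5% family-wise rate. It sets 0.05 as the level of a test and makes no claim across outcomes.

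**Conclusion.** The concern holds, with its size conditional. The plan as written does not control error across four listed primary outcomes. If one significant interaction on any of them is enough, the chance of at least one false-positive primary result under the global null is about 9–19%, roughly two to four times the per-test level. This assumes 14 completers per arm and a common between-outcome correlation of 0.9 down to 0. It rises to as much as 22.6% if the two calf levels are analysed separately, and falls if a Bonferroni-significant pair is also required.

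A reader might quote a firm 14–19%. That narrower range holds only for correlations up to about 0.7 and for the any-one-interaction rule, and the documents establish neither.

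**What to change.** Make the change before any unblinded analysis, as a dated amendment to both the protocol and the registry entry. The date matters because the trial was registered in July 2024 and section 2.1 describes recruitment in the past tense.

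**Preferred: one primary outcome at one time point.** The other three become key secondary outcomes. Which one leads is for the investigators to decide. Thigh CSA at Week 12 is one candidate: it is measured by CT and does not depend on effort, whereas grip and MVC require maximal effort from women who know whether they trained. Section 2.8 should then name the single test that decides the primary question, and section 2.7 should name the outcome it is sized for. Alpha stays at 0.05. The cost is wording, plus less formal weight for the demoted outcomes.

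**Alternative: keep all four as primary.** Apply Holm across the four Week 12 tests, say how calf levels and hands reduce to one variable each, and restate the power. This is more than a wording change. At the first-step alpha of 0.0125, power for f = 0.4 is about 37% with 42 women and 51% with 54, and 95% power would need 132.

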**Discussion:**

We have combined central and peripheral motor activation methods for the first time, attempting to use BFRT in combination with rTMS intervention to recruit more motor units by increasing motor cortex excitability, thereby enhancing skeletal muscle motor ability under BFRT and examining the intervention effects on skeletal muscle mass and strength in postmenopausal women. This will provide a new paradigm for healthy intervention in the skeletal muscles of postmenopausal women.

**Clinical Trial Registration:**

http://www.chictr.org.cn, Chinese Clinical Trial Registry ChiCTR2400086697.

## Introduction

1

Skeletal muscle is the fundamental driving force for maintaining muscle tone, preserving body posture, and accomplishing various physical activities, while also playing a crucial role in metabolism (1).With advancing age, the physical functions of middle-aged and elderly individuals gradually decline, including skeletal muscle mass and strength (2).This decline in muscle function and physical activity capacity appears more pronounced in older women. During the aging process, women inevitably experience the menopausal transition, leading to abrupt changes in hormone levels, particularly estradiol (3, 4). Estradiol is responsible for regulating the menstrual cycle and developing and maintaining female secondary sexual characteristics. It also promotes muscle health by enhancing muscle regeneration and stimulating the proliferation of muscle satellite cells (5, 6). Therefore, this hormonal shift is believed to impact the entire body, especially skeletal muscle composition, causing older women to accumulate more adipose tissue while gradually losing total muscle mass (7, 8). Previous studies have shown (9, 10) that postmenopausal women experience faster declines in muscle mass, muscle strength, and bone mineral density than age-matched men, making them more susceptible to chronic diseases such as osteoporosis and sarcopenia. As an age-related systemic and progressive skeletal muscle disorder, sarcopenia is characterized by generalized loss of muscle mass, reduced muscle strength, and impaired physical function (11). It is closely associated with adverse outcomes such as falls, fractures, physical disability, and even mortality (12, 13), emerging as one of the most common and critical diseases affecting mobility in older adults. Additionally, our previous research has found (14), a significant interaction between menopausal status and sarcopenia on cardiovascular disease (CVD) risk, where postmenopausal women with sarcopenia face a higher risk of CVD. Therefore, implementing proactive interventions for skeletal muscle in menopausal women to prevent or delay the onset of sarcopenia is of great medical and social significance for improving the health and quality of life in older women.

It is currently widely recognized that exercise intervention is a key measure for preventing and treating the decline in skeletal muscle mass and strength (15). Among these, resistance training is an effective method for preventing and treating the decline in skeletal muscle mass and strength, as it can enhance skeletal muscle strength through mechanisms such as regulating protein metabolic balance and reducing mitochondrial aging (16). Research has shown that high-intensity resistance training is more effective in alleviating sarcopenia in older people (17, 18), However, studies also point out that older people may not be able to tolerate the stress imposed by high-intensity resistance training on connective tissue, bones, and joints, which can lead to adverse reactions and increase the risk of injury (19), as a result, they often struggle to achieve the recommended exercise intensity and load (20). Therefore, new methods and approaches are needed to enhance the safety and adherence of exercise interventions for older people while achieving intervention effects comparable to those of high-intensity resistance training.

In recent years, blood flow restriction combined with low-intensity resistance training (LI-BFRT) has garnered increasing attention (21, 22). BFRT is a functional rehabilitation method that uses tourniquets or similar devices to apply pressure to the proximal end of the limbs, thereby restricting venous blood return to the distal end. This method effectively stimulates skeletal muscle growth, enhances skeletal muscle adaptability, improves muscle strength, inhibits muscle atrophy, improves blood circulation, and optimizes skeletal muscle capillary distribution, thereby promoting skeletal muscle functional rehabilitation (23, 24). Previous studies have confirmed that combining blood flow restriction with low-intensity resistance training (20%–30% of one-repetition maximum [1RM]) is an effective intervention for stimulating muscle fiber thickening and strength gains in older people, achieving effects similar to those of high-intensity resistance training (25), However, due to potential confounding factors associated with BFRT (such as gender and training volume) (19), further research is needed to provide evidence for the effective application of BFRT in older people (26). Although BFRT shows promising application potential, due to factors such as age and safety considerations, the blood flow restriction pressure and resistance load for postmenopausal women often cannot be set at higher levels, resulting in improvements in skeletal muscle mass and function, but these improvements still fall short of the effects achieved by high-intensity resistance training alone (27).

Research has shown that the increase in skeletal muscle strength during long-term training practice involves two aspects: adaptive hypertrophy of muscle fibers (peripheral factors) and an increase in the number of motor units recruited by the nervous system (central factors). In recent years, the causes of sarcopenia associated with age-related deterioration of nervous system function have attracted the attention of researchers (28, 29). During the normal aging process, the motor cortex undergoes significant morphological changes (30). Recent studies suggest that age-related diseases such as sarcopenia may be caused by cortical atrophy, reduced cortical output, motor neuron apoptosis, decreased action potential frequency, reduced recruitment of motor units, and alterations in neuromuscular junctions associated with neurons (31, 32).

Transcranial magnetic stimulation (TMS) is a magnetic stimulation technique based on the principles of electromagnetic induction and conversion. It employs time-varying magnetic fields to stimulate the cerebral cortex and peripheral nerves, inducing currents that alter the action potentials of neurons. This process influences neurotransmitter metabolism and neural electrical activity within the brain, thereby triggering a series of physiological and biochemical responses (33). It has been used in the treatment of neurological and psychiatric disorders associated with excitatory dysfunction of the brain, with rTMS commonly employed to modulate cortical excitability, as reflected by changes in motor-evoked potentials (MEPs). In interventions targeting post-stroke motor function, studies have found that rTMS can significantly alter motor cortex excitability and plasticity (34), optimize motor cortex plasticity changes induced by motor training, improve limb motor function (35, 36), and enhance the long-term effects of motor training in stroke patients. Currently, there are no reported applications of rTMS for interventions targeting individuals with reduced skeletal muscle mass and strength or sarcopenia, particularly postmenopausal women.

In summary, this study aims to investigate the effects of a 12-week LI-BFRT combined with rTMS intervention on skeletal muscle mass and strength, as well as physical function, in postmenopausal women. It will also quantitatively analyze changes in motor cortex excitability related to neuromuscular activity and hematological parameters before and after the exercise intervention, exploring potential mechanisms. Our findings will provide new insights and experimental evidence for effectively preventing or delaying the onset and progression of sarcopenia in older women.

## Methods and analysis

2

### Study design

2.1

This is a 12-week, single-center, single-blind randomized controlled trial study. This study has been approved by the Ethics Committee of Shanghai University of Sport (Approval Number: 102772024RT078) and registered in the China Clinical Trial Registry (Registration Number: ChiCTR2400086697, registered on July 9, 2024). All participants provided written informed consent prior to enrollment. The study was conducted in accordance with the Declaration of Helsinki. The experimental flowchart is shown in Figure 1.

**Figure 1 F1:**
[figure not shown]
Flow chart showing the participant recruitment, intervention and assessment process. LI-BFRT, low intensity-blood flow restriction training; rTMS, repetitive transcranial magnetic stimulation; 1RM, 1 repetition maximum.

This study recruited healthy postmenopausal women. After applying inclusion and exclusion criteria, eligible participants were randomly assigned to the rTMS + LI-BFRT group, LI-BFRT group, and control group in a 1:1:1 ratio. Researchers confirmed the basic information of all participants who had signed informed consent forms (age, date of birth, contact information); after confirmation, blood samples were collected from participants, and height, weight, and body composition were measured. Subsequently, tests were conducted to assess skeletal muscle mass, skeletal muscle strength, motor cortex excitability, and motor performance. Participants in the two intervention groups received a 12-week supervised training intervention, three times per week. The control group was instructed to maintain their previous lifestyle and undergo a 12-week health education program, once per week. The program comprises weekly lectures on general health topics (nutrition, sleep hygiene, chronic disease awareness) and explicitly does not include active physical training or exercise prescriptions. All participants were assessed at three time points: pre-intervention (Week 0), post-intervention (Week 12), and at long-term follow-up (Week 24). The intervention and assessment schedule are outlined in Table 1.

**Table 1 T1:** The schedule of participant recruitment, intervention, and study assessment.

Variables	Recruitment and screening	Baseline assessment	Intervention (Week 1-Week12)		Follow-up assessment	Long-term Follow-up assessment
Time-point		Week 0	Week 4	Week 8	Week 12	Week 24
Information consent	X					
Inclusion and exclusion criteria	X					
Demographic data	X					
Randomization	X					
AOP test		X				
RMT test		X				
Resistance training load		X	X	X		
Primary outcomes						
Thigh muscle CSA		X			X	X
Calf muscles CSA		X			X	X
Hand grip strength		X			X	X
Knee extension MVC		X			X	X
Secondary outcome						
Body composition		X			X	X
5-times chair stand test		X			X	X
30-Second Chair Stand test		X			X	X
Timed Up and Go test		X			X	X
30-Second Arm Curl Test		X			X	X
MEPs test		X			X	X
Hematological parameters		X			X	X

AOP, arterial occlusion pressure; RMT, resting motor threshold; muscle CSA, muscle cross-sectional area; MVC, maximal voluntary contraction; MEPs, motor-evoked potentials.

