### Randomization and blinding

2.4

Participants meeting the inclusion and exclusion criteria will be randomly assigned to the rTMS + LI-BFRT group, LI-BFRT group, and control group at a 1:1:1 ratio. The randomization sequence will be generated by an independent statistician using a computer program with block randomization to ensure balanced sample sizes across groups throughout the enrollment process. Group allocation results will be concealed in numbered, sealed, opaque envelopes, which are stored and distributed by researchers not involved in recruitment, intervention, or assessment to achieve allocation concealment. Outcome assessors and data analysts will remain blinded to participants' group assignments throughout the study. Researchers implementing the intervention are required to withhold group information during assessments.

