### Interventions

2.5

Pre-intervention procedures: Before the intervention, participants in the rTMS + LI-BFRT and LI-BFRT groups underwent a one-repetition maximum (1RM) test and arterial occlusion pressure (AOP) measurement, and were trained to use the 6–20 Borg Rating of Perceived Exertion (RPE) scale to determine target resistance loads. Exercise loads were applied using appropriately weighted dumbbells. Missed sessions were rescheduled within the same week to maintain consistent intervention volume. All participants attended a pre-intervention orientation to familiarize themselves with the procedures.

Adherence and fidelity: All sessions were supervised by trained researchers. Attendance and completion of prescribed exercise sets were recorded digitally. Any missed sessions or protocol deviations were documented. Adherence was calculated as the percentage of completed sessions relative to the total prescribed, with an attendance rate of ≥ 80% considered a valid indicator of intervention effectiveness. Detailed intervention protocols for all groups are provided in Table 2.

**Table 2 T2:** Details of the three groups of protocol.

Weeks	Group	Specific intervention content	Sets	Repetitions	Interval rest time between sets	Intensity	Frequency
1–4	LI-BFRT	Seated biceps curl, Seated shoulder press Seated knee extension, Squat	4	12, 10, 10, 10	30s	Phase 1 20%1RM	3times/week
	rTMS + LI-BFRT	M1 area, at 10 Hz, 90%RMT, intermittent stimulation, a total of 2,000 pulses; LI-BFRT immediately after the stimulation ends.					
	CG	Education session (20 min)	/	/	/	/	1time/week
5–8	LI-BFRT	Seated biceps curl, Seated shoulder press Seated knee extension, Squat	4	12, 10, 10, 10	30s	Phase 2 25%1RM	3times/week
	rTMS + LI-BFRT	M1 area, at 10 Hz, 90%RMT, intermittent stimulation, a total of 2,000 pulses; LI-BFRT immediately after the stimulation ends					
	CG	Education session (20 min)	/	/	/	/	1time/week
8–12	LI-BFRT	Seated biceps curl, Seated shoulder press Seated knee extension, Squat	4	12, 10, 10, 10	30s	Phase 3 30%1RM	3times/week
	rTMS + LI-BFRT	M1 area, at 10 Hz, 90%RMT, intermittent stimulation, a total of 2,000 pulses; LI-BFRT immediately after the stimulation ends					
	CG	Education session (20 min)	/	/	/	/	1 time/week
M1 area: primary motor cortex							

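### Randomisation is scheduled before the Week 0 outcome tests, and nothing says women stay unaware of their arm until baseline is complete, so effort-dependent baselines may differ by arm

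*Protocol article*

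**What the plan says.** The order of steps appears twice in section 2.1.

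- **Narrative.** It states: "After applying inclusion and exclusion criteria, eligible participants were randomly assigned to the rTMS + LI-BFRT group". Confirmation of personal details, blood sampling, height, weight and body composition follow, and then: "Subsequently, tests were conducted to assess skeletal muscle mass, skeletal muscle strength, motor cortex excitability, and motor performance".
- **Table 1** ("The schedule of participant recruitment, intervention, and study assessment"). Randomisation is marked in the recruitment and screening column. Every primary and secondary outcome is first marked one column later, at Week 0.

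On blinding, section 2.1 calls the study a "single-center, single-blind randomized controlled trial study". Section 2.4 names who is blinded: "Outcome assessors and data analysts will remain blinded to participants' group assignments throughout the study". It adds two safeguards: "Group allocation results will be concealed in numbered, sealed, opaque envelopes", and "Researchers implementing the intervention are required to withhold group information during assessments".

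Section 2.5 describes tests specific to two arms before the intervention: "participants in the rTMS + LI-BFRT and LI-BFRT groups underwent a one-repetition maximum (1RM) test and arterial occlusion pressure (AOP) measurement". Table 1 places the AOP test and the training load at Week 0.

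Grip strength and knee-extension MVC are primary outcomes measured at maximal effort (section 2.6.1.2). The main analysis is a time × group repeated-measures ANOVA in which baseline is one of three time points (section 2.8).

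**The concern.** A baseline value protects a comparison only if it cannot be affected by allocation. Here the schedule puts allocation first. The arms (brain stimulation plus cuffed training, cuffed training alone, weekly lectures) are easy for a participant to tell apart, and no sham is described. Blinding the assessor does not stop a woman who knows her arm from trying more or less hard.

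Four kinds of outcome depend on effort: grip, knee-extension MVC, the chair-stand and timed up-and-go tests, and the arm curl. If effort at Week 0 differs by arm, the difference becomes part of the estimated change. Lower baseline effort in a training arm would exaggerate its gain, and higher effort would hide some of it. The direction cannot be known in advance.

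**Working it through.** The point concerns the order of procedures, so the protocol states no figure to reproduce. The relevant sections are compared first. The arithmetic after that is illustrative only.

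**1. Order and disclosure**

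- Section 2.1 and Table 1 agree that assignment precedes the outcome tests.
- The envelopes in section 2.4 conceal the sequence until assignment. The section does not say when an envelope is opened, or when a woman is told, relative to Week 0.
- The duty to withhold group information falls on the staff who deliver the intervention. It protects assessors and does not say that participants are kept unaware.
- The 1RM and AOP tests are for the two training arms only, so they could separate training from control. They cannot separate the two training arms from each other. Section 2.5 places them before the intervention, and their order relative to the Week 0 outcome tests is not fixed.

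**2. Outcomes exposed**

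Table 1 has four primary rows. Two depend on effort (grip, knee-extension MVC) and two do not (thigh and calf CSA by CT). Among the secondary outcomes, the four physical performance tests depend on effort. Body composition, resting MEPs and blood markers largely do not.

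**3. Size against the design effect**

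Input: f = 0.4 (section 2.7). Assumptions: three evenly spaced means (−d, 0, +d), and the shift expressed in the same SD units.

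- f = d × √(2/3), so d = 0.4 / 0.816 = 0.49 SD between adjacent arms.
- Extreme arms: 2 × 0.49 = 0.98 SD.
- Assumed shift of 0.1 SD: 0.1/0.49 = 20% of the adjacent step; 0.1/0.98 = 10% of the extreme difference.
- Assumed shift of 0.2 SD: 0.2/0.49 = 41%; 0.2/0.98 = 20%.

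**4. How the shift reaches the analysis**

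If observed baseline effort in one arm is lower by b SD and follow-up is unaffected, the between-arm difference in change from Week 0 is biased by b. With baseline as a covariate the bias is about ρ × b, where ρ is the baseline to follow-up correlation. This was simulated with two arms of 18 (the planned group size), no true effect and 4,000 runs per setting. Both b and ρ are assumed.

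| ρ | b (SD) | Bias, change score | False-positive rate | Bias, baseline-adjusted | False-positive rate |
|---|---|---|---|---|---|
| 0.7 | 0 | 0.00 | 0.05 | 0.00 | 0.05 |
| 0.7 | 0.1 | 0.10 | 0.07 | 0.07 | 0.06 |
| 0.7 | 0.2 | 0.20 | 0.11 | 0.14 | 0.09 |
| 0.7 | 0.3 | 0.30 | 0.20 | 0.20 | 0.12 |
| 0.9 | 0 | 0.00 | 0.05 | 0.00 | 0.05 |
| 0.9 | 0.1 | 0.10 | 0.10 | 0.09 | 0.09 |
| 0.9 | 0.2 | 0.20 | 0.25 | 0.18 | 0.21 |
| 0.9 | 0.3 | 0.30 | 0.51 | 0.27 | 0.43 |

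The rows with b = 0 show the position when baseline is measured before allocation is known: no bias by this route and the nominal error rate.

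**The case against.** The strongest reply is that bias requires women to know their arm before testing, and the document does not say that they do. Allocation is held in sealed envelopes by staff independent of recruitment, intervention and assessment. Figure 1, which is not shown here, might settle the order. The narrative is also not a strict chronology: it mentions confirming personal details after assignment, whereas Table 1 puts consent and demographic data at screening. This stands as a limit on the claim. It does not remove the concern, because Table 1 gives the same order on its own and no sentence keeps participants unaware until baseline is done.

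Three stronger readings are tempting, and the document supports none of them.

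- A reader might infer that 1RM testing reveals the arm, or gives the training arms practice before baseline. At most it separates training from control, and its place within Week 0 is not stated. It therefore says nothing about the comparison that isolates rTMS. Any practice from 1RM testing before Week 12 would remain after reordering.
- A reader might infer that women lost between randomisation and Week 0 undo the randomised comparison. The article gives neither that interval nor any expected loss, and the handling of such women may be set out elsewhere.
- A reader might take the 41% as an estimate of bias. The shift has no source in the document, and against the extreme arms the same shift is 20%.

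**Conclusion.** The concern holds in a limited form. The stated sequence leaves open a route by which knowledge of the arm could alter baseline effort, and the blinding provisions do not close it. The article does not show that women knew their arm or that the strength results will be biased.

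The point applies to two of the four primary outcome rows and to the physical performance tests. CT muscle CSA and the other non-effort measures are largely untouched. The size is unknown. At an assumed 0.1–0.2 SD it would be 20–41% of the adjacent-arm step, or 10–20% of the extreme-arm difference.

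These figures assume evenly spaced means at f = 0.4, a common SD, and a shift confined to Week 0. If effort shifted equally at follow-up, the two shifts would cancel in the change. Effort differences at follow-up are a separate matter that the timing of randomisation cannot cure. Baseline adjustment would reduce the bias, but by little when baseline and follow-up are highly correlated. Because the remedy is cheap, the change should be made even though the size cannot be established.

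**What to change.** Move the randomisation mark in Table 1 to after the Week 0 assessments and reorder section 2.1 to match: consent, screening, all Week 0 outcome tests, opening of the envelope, then the arm-specific 1RM and AOP tests. State in section 2.4 that a woman is told her arm only after her baseline outcomes are recorded.

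The sample size and the set of assessments do not change. The small cost is that the 1RM and AOP tests must be scheduled after the outcome tests, which may constrain how the Week 0 visit is arranged.

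Parts of the article are in the past tense, so enrolment may already have taken place. In that case, report when women learned their allocation relative to Week 0 testing, and how many were tested after learning it. If women were in fact told only after baseline, correcting Table 1 and section 2.1 to say so resolves the point.
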